^ and mood disorders particularly [e.g.,
60,
61]. The present project uses three complementary frameworks to advance prediction of BD course from RAR – statistical risk (Cox Survival Analysis), probabilistic network graphs (Dynamic Bayesian Network Analysis) and non-linear dynamic analysis (Hadaeghi’s Complex System Model of BD,
19). The RAR measures to be modelled as predictors in these analyses include the three non-parametric Van Someren variables (above). Relative Amplitude is elevated as a correlate of circadian biology in the mechanistic investigation of Study 2 (see below).

*Actigraphic Measurement of the 24-h Rest-Activity Rhythm can Predict Course of BD*

A substantial body of research has investigated
*cross-sectional
* associations between actigraphy-measured RAR variables and BD phenotypes. A recent systematic review identified 70 studies investigating RAR via actigraphy in BD samples.
^
16
^ Attenuated amplitude of RAR has been shown to associate with several BD phenotypes.
^
62
^
^–^
^
64
^ Consistent with the circadian robustness hypothesis (above), the largest study to date
^
31
^ found that a one quintile (20%) decrease in Relative Amplitude was associated with a small but significant increased risk of lifetime major depressive disorder (OR 1.06, 95% CI 1.04–1.08) and lifetime BD (OR 1.11, 1.03–1.20) [
1].

Several groups have argued for the potential of RAR signals to generate a clinically-useful predictive algorithm of short-term course in mood disorders and BD specifically.
^
10
^
^,^
^
16
^
^,^
^
18
^
^,^
^
43
^
^,^
^
66
^
^–^
^
68
^ Prospective empirical investigations are limited to date, but an illustrative example is the study of Ferrand and colleagues, in which RAR was sampled with 14 days actigraphy data before 69 euthymic individuals with BD were prospectively tracked for a median duration of 3.5 years.
^
69
^ Approximately 65% of participants experienced a relapse or recurrence during follow-up. After adjusting for key clinical variables (age, sex, BD subtype, number of mood stabilisers, etc.), time to episode onset was predicted by an actigraphy dimension comprising amplitude and variability/stability of circadian rhythms (
*p* = 0.009). The area under the curve (AUC) was improved from 0.64 for clinical predictors alone to 0.82 with the addition of actigraphy-derived Intradaily Variability (
*p* = 0.04).

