### Modelling approaches

2.6

As noted above, it is not possible to present a detailed statistical analysis plan until the data to be analysed is clear. Here, we overview data preprocessing plans, present a power analysis for Study 1, and overview the three planned analytic approaches.

*Data preprocessing*

Two categories of missing data will be identified and managed using tailored approaches. For actigraphy data, short and scattered gaps, where the device is worn but a few data points are missing, will be imputed using forward- and backward-fill (FFill/BFill) methods, which are suitable for brief intervals. Longer and continuous gaps, arising from non-wear periods such as device charging or participant non-adherence, will be addressed using a subject-specific model that combines a circadian baseline estimating expected activity at each clock time with a recurrent neural network (RNN) that models short-term deviations from this baseline. A gating mechanism will determine the weighting between these components according to the duration of the gap, giving greater weight to the baseline for longer periods. All imputed data points will be flagged for potential exclusion in sensitivity analyses.

Missingness in clinical data will be handled according to analytic role: participants missing essential outcomes (e.g., relapse status) will be excluded from analyses requiring those outcomes. Clinical predictors and covariates will not be imputed; analyses will use available-case data. Patterns and proportions of missing data will be reported, and sensitivity analyses will assess the robustness of study findings.

*Power Analysis*

Based on the effect size identified by Ferrand et al (see above), a one standard deviation increase in the actigraphy measure increases the risk of relapse by 57% (Hazard Ratio = 1.57). Assuming a sample size of
*N* = 100 participants, initially assuming zero drop-out and then 20% drop-out (
*N* = 80) we used simulation to calculate power estimates based on different Hazard Rate assumptions for a Cox Survival Analysis in Study 1. First, a sample of
*N* = 100 provides 90.6% power to detect a 57% increase in the relative risk of relapse while a sample size of
*N* = 80 provides 75.6% power to detect such an increase. Second, a sample of
*N* = 100 provides 83.0% power to detect a 49% increase in the relative risk of relapse while a sample size of

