*N* = 80 provides 83.8% power to detect a 65% increase in the relative risk of relapse. This suggests that even with a 20% dropout the study is nearly sufficiently powered to detect the expected relative risk of relapse (Hazard Ratio = 1.57) and powered to detect a slightly higher relative risk of relapse (Hazard Ratio = 1.65). Note also that the selected sample sizes of
*N* = 100 people with BD in Study 1, 50 in Study 2 (25 BD, 25 matched controls), and 45 in Study 3 (15 manic and 30 depressed) were pragmatic maxima. Recruitment beyond these pragmatic maxima will continue if resourcing permits.

*Cox Survival Analysis*

Cox Survival Analysis will be employed with Elastic Net
^
97
^ to determine variables to include. Relative Amplitude, Intradaily Variability, Interdaily Stability will be included as predictors in a random effects or frailty model of survival time to relapse (across the three epochs of Study 1 and the single epoch of Study 2). Initial time to first episode analysis: Proportional Hazards (Cox) regression with the five clinical covariates listed above. For the modelling of recurrent episodes a Prentice-Williams-Prentice (PWP) model will be used rather than a frailty model because the PWP is appropriate when only a small number of events is likely.
^
98
^

To model the relationship between the actigraphy signal and time to first episode, a two-stage joint survival model will be used. These models analyse time-to-event outcomes that may be linked to biomarkers that are repeatedly measured. A two-stage joint survival model analyses time-to-event outcomes influenced by a longitudinal, time-varying biomarker by fitting two separate models in sequence: a longitudinal model for the biomarker and a survival model for the event. This is a computationally efficient alternative to fully joint models, which can be very time-consuming to fit. The main drawback is that standard two-stage methods can disregard the uncertainty from the first stage’s estimates when they are used in the second, though advanced methods use techniques like multiple imputation to account for this.
^
99
^

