^ For example, the total number of participants (
*N* = 100 at baseline) for modelling relapse events in Study 1 is small: A commonly cited prospective study estimates individuals with BD I experience 0.4 new episodes per annum on average,
^
114
^ so we estimate only approximately 60 relapses will be observed. Replication of the project’s findings in unseen data sets is therefore essential. We are in discussion with teams worldwide for data sharing to support these tests. For example, we have had discussions with, (i) another Wellcome-funded project collecting RAR data via actigraphy in a large prospective sample of BD
https://wellcome.org/research-funding/funding-portfolio/funded-grants/ambient-and-passive-collection-sleep-and-circadian (ii) the BD2 consortium which is collecting RAR via Fitbit in a large prospective study of people diagnosed with BD-I
https://www.bipolardiscoveries.org/our-work/integrated-network/.

Several strategies are embedded to mitigate the sample size constraint and maximise the project’s value. First, the high-resolution nature of actigraphy (> one million data points per epoch per participant) is leveraged to support modelling within-subject dynamics. Second, Study 1 collects three distinct monitoring epochs per participant, increasing the number of analytic events available for intra-individual analyses. Finally, the inclusion of the simple, widely used Van Someren variables provides a crucial anchor to large cross-sectional datasets (e.g., UK Biobank), allowing for contextualisation and comparison of our prospective findings.

The project’s findings may have several implications. First and foremost, if a predictive algorithm of relapse risk can be identified and subsequently replicated in independent samples, the project will have made a step towards an automated forecasting tool for BD [as being trialled for people living with epilepsy,
102]. Beyond providing early warning advice, such an indicator may play a more positive role in BD management, by minimising treatment burden. For example, such a tool could play a part in deciding who may not require ‘infinite maintenance treatment’ for their BD.
^
115
^

Secondly, the project will generate an entirely novel network model of the relationship between RAR, sleep and circadian parameters as predictors of relapse in BD. As argued in a recent expert report, mechanistic understanding of SCRD in mental health is lacking.
^
35

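### The four Study 1 power figures cannot all hold under one event rate with 20% drop-out applied once, and they are not reconciled with the relapse count in the Discussion

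*Protocol article*

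**What the plan says.** The Power Analysis in section 2.6 takes a hazard ratio of 1.57 per standard deviation of the actigraphy measure from a cited cohort study. It then simulates a Cox analysis for Study 1, "initially assuming zero drop-out and then 20% drop-out", that is, N = 100 and N = 80. Four results follow:

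- N = 100, HR 1.57: "provides 90.6% power to detect a 57% increase in the relative risk of relapse"
- N = 80, HR 1.57: "provides 75.6% power to detect such an increase"
- N = 100, HR 1.49: "provides 83.0% power to detect a 49% increase in the relative risk of relapse"
- N = 80, HR 1.65: "provides 83.8% power to detect a 65% increase in the relative risk of relapse"

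From these the article concludes that, even after 20% drop-out, the study comes close to adequate power for HR 1.57 and has adequate power for HR 1.65. The paragraph gives no alpha, sidedness, baseline hazard, expected number of events or number of simulation replicates.

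The Discussion (section 3) cites 0.4 new episodes per year in BD I, "so we estimate only approximately 60 relapses will be observed". Section 2.2 gives a follow-up window of 78 weeks. The Abstract and the first Cox analysis in section 2.6 use time to first relapse.

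**The concern.** In a Cox analysis with a given predictor, power depends on the number of events and the hazard ratio. If drop-out only takes the sample from 100 to 80, the event count should fall by the same 20%. The stated loss at HR 1.57, from 90.6% to 75.6%, is larger than that.

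This is the only power justification in the article, and it supports an explicit statement of adequacy for a primary-aim analysis. If the N = 100 event fraction is right, power after drop-out is already above 80% and the adequacy sentence is too cautious. If the N = 80 fraction is right, the no-drop-out figures are too high. A reader cannot tell which applies, and so cannot judge how a null result for the rest-activity variables should be read.

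**Working it through.** **Inputs.** HR, N and power from section 2.6; 78 weeks (1.5 years) from section 2.2; 0.4 episodes per year and 60 relapses from section 3. Assumed: a single standardised predictor and two-sided 5% (z = 1.960), with other levels tried below.

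**Step 1: events implied by each stated figure.** The Schoenfeld formula for a covariate with SD 1 is power = Φ(√D × ln HR − z), so D = ((z + z_power) / ln HR)².

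| N | HR | ln HR | Stated power | z_power | Implied D | D/N |
|---|---|---|---|---|---|---|
| 100 | 1.57 | 0.4511 | 90.6% | 1.317 | 52.8 | 53% |
| 100 | 1.49 | 0.3988 | 83.0% | 0.954 | 53.4 | 53% |
| 80 | 1.57 | 0.4511 | 75.6% | 0.694 | 34.6 | 43% |
| 80 | 1.65 | 0.5008 | 83.8% | 0.986 | 34.6 | 43% |

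Within each sample size the two figures agree closely; between sample sizes they do not. Losing 20% of participants takes 53 events to 0.8 × 53 = 42.4, not 34.6.

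**Step 2: put both sample sizes on one event fraction.**

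- Common 53%: N = 100 gives 90.7% and 82.7%, which reproduces the stated pair. N = 80 (42.4 events) gives 83.6% and 90.3%, against 75.6% and 83.8% stated.
- Common 43.3%: N = 80 gives 75.6% and 83.8%, which reproduces the stated pair. N = 100 (43.3 events) gives 84.3% and 74.7%, against 90.6% and 83.0% stated.
- Best single compromise, 47.9%: the four figures are missed by 2.9, 4.2, 4.1 and 3.5 points (N = 100 HR 1.57, N = 100 HR 1.49, N = 80 HR 1.57, N = 80 HR 1.65). Both N = 100 values come out too low and both N = 80 values too high.

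**Step 3: does the assumed alpha create the split?** No. At one-sided 5% (z = 1.645) the implied events are 43.1 and 42.5 at N = 100 (about 43%) and 26.9 and 27.6 at N = 80 (about 34%). At two-sided 1% the fractions are 75–78% against 63–66%.

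**Step 4: could it be simulation noise?** The 95% margin is 1.96 × √(p(1−p)/n). With 1000 replicates it is 1.8 to 2.7 points across the four figures. With only 500 it is 2.6 (90.6%), 3.3 (83.0%), 3.8 (75.6%) and 3.2 (83.8%). Each miss in the best compromise exceeds its own margin in both cases. The replicate numbers are assumptions, as the article gives none.

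**Step 5: compare with the Discussion.** 0.4 × 1.5 × 100 = 60 is a count of all episodes, repeats included. Under a constant hazard, the proportion with a first relapse in 78 weeks is 1 − exp(−0.6) = 45.1%, or 45.1 events at N = 100 and 36.1 at N = 80. At two-sided 5%:

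| N | HR | Stated | At 0.4 per year, first relapse | Cox simulation, 4000 replicates |
|---|---|---|---|---|
| 100 | 1.57 | 90.6% | 85.8% | 84.6% |
| 100 | 1.49 | 83.0% | 76.4% | 76.3% |
| 80 | 1.57 | 75.6% | 77.3% | 75.4% |
| 80 | 1.65 | 83.8% | 85.3% | 84.3% |

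The simulation used exponential times, a standard normal predictor, censoring at 1.5 years and a Wald test. At one-sided 5% the same event counts give, in table order, 91.7%, 84.9%, 85.7% and 91.4%.

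**The case against.** The strongest reply is that the inputs are undisclosed, so no single stated figure can be called wrong. That stands. A reader might infer from Step 5 that the N = 100 power is overstated, about 86% rather than 90.6%. The documents do not support this as a firm conclusion, for four reasons:

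- Alpha is not stated. At one-sided 5% and 0.4 per year, the N = 100 pair roughly fits and the N = 80 pair is too low.
- The 0.4 rate is a BD I figure from the Discussion and is not named as a power input. Study 1 also enrols BD II and counts hypomanic episodes, so its rate could be higher.
- If all 60 relapses counted as events, N = 100 at HR 1.57 would give 93.7%, above the stated value. Recurrent-event models are also planned.
- The adequacy sentence rests on the N = 80 figures, and these are not overstated at 0.4 per year.

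A single event rate can also be rescued by a different mistake. If the 20% loss was taken twice (0.8 × 80 = 64 analysed), one fraction of 53.6% reproduces all four figures within 0.4 points at two-sided 5%. This is a possible cause that cannot be proved from the text; if it is the cause, the drop-out figures are too low.

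The paragraph does say that hazard-rate assumptions were varied. But the results vary only N and the hazard ratio. If the baseline hazard also changed with N, the comparison is no longer one of drop-out.

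Two further inferences go beyond the text. The article does not say that HR 1.57 belongs to a composite actigraphy dimension rather than a single variable. It also gives no basis for a particular loss of power from correlated covariates. Finally, the project calls itself exploratory, describes its sample sizes as pragmatic maxima and names the small number of data points as its main limitation. That lowers the stakes but does not make the four figures agree.

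**Conclusion.** The inconsistency holds. With drop-out applied once, no single event fraction reproduces all four figures at any significance level tried. The gap is about 10 percentage points in event fraction (53% against 43% at two-sided 5%; 43% against 34% at one-sided 5%), worth 6 to 8 points of power in whichever pair is put on the other's footing. Which pair is wrong, and therefore whether power is over- or understated, is not determined by the document.

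The lack of reconciliation with the Discussion also holds: 60 total episodes correspond to about 45 first relapses at N = 100 and 36 at N = 80, given 0.4 per year and a constant hazard. The power values at those counts (about 86%, 76%, 77% and 85% in the order of Step 5) are conditional on two-sided 5% and a single predictor.

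Two scenarios serve as sensitivity ranges only. In the cohort that supplied the effect size, "Approximately 65% of participants experienced a relapse or recurrence during follow-up" (median 3.5 years). Treating that median as everyone's exposure gives −ln(0.35)/3.5 = 0.30 per year, a first-relapse fraction of 1 − exp(−0.45) = 36%, and about 77% (N = 100) and 68% (N = 80) power for HR 1.57. If other covariates explained 20–30% of the predictor's variance (an assumption), power at 0.4 per year would be 77–72% and 68–62%.

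**What to change.** Re-run all four figures with one baseline hazard for both sample sizes, 78-week censoring, time to first relapse and drop-out applied once. State alpha, sidedness, baseline hazard, drop-out handling and number of replicates. Report the expected first relapses at each sample size separately from the 60 total episodes, and say how the chosen hazard relates to 0.4 per year. Replace 90.6%, 75.6%, 83.0% and 83.8% with the results, and align the adequacy sentence at the end of the Power Analysis with them, whichever way they move. A range over 0.30 to 0.40 per year, and a run with the planned covariates, would be useful as sensitivity analyses.

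The cost is one re-run of an existing simulation and a revised paragraph. No participants, visits or design features change.

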The primary aim of this project is to develop an SCRD-informed, RAR based algorithm forecasting relapse risk in BD. Confidence in the reliability and generalisability of a predictive algorithm would be strengthened with improved mechanistic understanding of SCRD in BD as measured by RAR in this forecasting context. Consequently, the project’s secondary aim is to contribute to mechanistic understanding by, (i) investigating molecular biological correlates of RAR parameters, and (ii) exploring system instability as a predictor of both relapse into, and recovery from acute episodes (with both phenomena understood as transitions in state space [e.g.,
19]).

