**Figure 2. f2:**
[figure not shown]
Study 2 design overview.

Three research questions and two hypotheses are therefore set for Study 2:
•Research Question 1: Does the Cox Survival Analysis model derived in Study 1 replicate amongst
*N* = 25 BD participants in an LMIC cohort?•Research Question 2: Does Dynamic Bayesian Network Analysis enable examination of relapse prediction amongst
*N* = 25 BD participants in an LMIC cohort?•Research Question 3: Does Hadaeghi’s Complex System Model of relapse prediction derived in Study 1 replicate amongst
*N* = 25 BD participants in an LMIC cohort?•Hypothesis 1: Amongst the complete sample (
*N* = 50), Relative Amplitude will correlate with the diurnal amplitude of both circadian gene expression and blood metabolites.•Hypothesis 2: Diurnal amplitude of circadian gene expression and blood metabolites, and Relative Amplitude will be attenuated in people with interepisode BD (
*N* = 25) compared to age, gender, and employment-matched healthy controls (
*N* = 25).

*Study 3: Exploring generalisability of the Complex System model of state transition from relapse prediction to treatment response.*

Study 3 contributes to the project’s secondary mechanistic aim by investigating if complex system features found in Study 1 to predict relapse (state transition into an episode) generalise to prediction of treatment response from an acute episode (state transition to recovery). If generalisation is demonstrated, it could be hypothesised that Hadaeghi’s Complex System Model captures generic system instability (as opposed to a relapse-specific process).

The primary aim of Study 3 is therefore to investigate whether the relapse risk algorithm informed by Hadaeghi’s Complex System Model (trained and tested on Study 1 data) can be extended to response to treatment.
^
19
^ The state transition of Study 3 is measured in binary response to treatment. Response to treatment at 8 weeks is operationalised as 50% reduction in MADRS (for those in depressive episode at baseline) or 50% reduction in YMRS (for those in manic episode at baseline). Participants will wear actigraphs for 21 days – for consistency with Study 1 and 2, the first 14 days only will be used in modelling of binary response to treatment.
Figure 3 below summarises the study design for this primary aim.

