**Figure 3. f3:**
[figure not shown]
Study 3 design overview.

Study 3 has two additional aims related to improved characterisation of associations between RAR signals and short-term mood dynamics. The secondary aim of Study 3 is to examine the effect of baseline episode polarity—that is, whether the acute episode is depressive or manic—on the performance and structure of the predictive model. The analysis of Study 3’s secondary aim will investigate whether polarity moderates model accuracy against the binary outcome of 50% reduction in symptoms at 8 weeks, using 14 days’ actigraphy data. To increase the granularity of the investigation of this state transition, a tertiary aim of Study 3 is to explore temporal patterns in weekly RAR in relation to weekly clinician ratings of mood (MADRS, YMRS) and clinical state (CGI). The process-focus of this exploratory analysis takes advantage of the full 21 days of actigraphy.

Study 3 therefore investigates the prediction of acute treatment response from RAR variables amongst people who are experiencing a severe episode of BD [an important clinical question in its own right,
78]. Participants will be individuals with BD receiving guideline-based care and treatment
^
75
^ for acute manic (
*N* = 15) or bipolar depressive (
*N* = 30) episodes (on an inpatient, outpatient, or hybrid basis). Participants will be patients of Te Whatu Ora-Waitaha Canterbury Mental Health Services.

Three research questions address the development and testing of a state transition model, and its potential moderation by baseline episode polarity.
•Research Question 1: How many additional samples (
*x*) from the
*N* = 45 Study 3 sample are required to retrain the Study 1 complex system model predicting relapse (
*N* = 75) to achieve acceptable prediction accuracy for
*a state transition model* predicting both relapse amongst interepisode patients and response to treatment amongst acutely ill patients?•Research Question 2: Can a complex system model of state transition trained on
*N* = 75 Study 1 samples and
*x* (from Research Question 1) Study 3 samples predict state transition in an unseen data set of
*N* = 25 Study 1 samples and N = (45 –
*x*) samples from Study 3?•Research Question 3: Is episode polarity at baseline in the Study 3 cohort (
*n* = 30 depression versus
*n* = 15 manic) a moderator for the models developed in Research Question 1 and Research Question 2?

*Work Package 4: Integrative Data Synthesis*

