101]. In addition to Dynamic Bayesian Network Analysis, other machine learning frameworks that complement causal inference with predictive performance will be explored. Specifically, ensemble-based models such as Gradient Boosting Machines and Random Forests, and regularised regression approaches such as LASSO or Elastic Net, will be considered to identify combinations of RAR features that best predict relapse or treatment outcomes.

*Hadaeghi’s Complex System Model of BD*

A key clinical challenge in predicting the course of BD is the condition’s dramatic state changes, most commonly discussed in relation to switching.
^
102
^ It has been proposed that switching and other nonlinear patterns in the course of BD are best understood from a complex system viewpoint, as clinically critical transitions in state space.
^
68
^
^,^
^
103
^ From this perspective, relapse into a new episode and recovery from an acute episode both represent state transitions at which interacting biological and behavioural processes lose or regain stability, and the system shifts to a new state.

Importantly for the theoretical coherence of the present SCRD-grounded project, Hadaeghi’s Complex System Model conceptualises BD as the interaction between two coupled subsystems: the circadian pacemaker and the frontal–limbic system, which governs emotional regulation and behavioural activation. Feedback between these subsystems can maintain stable oscillations (corresponding to episode stability) or, under certain conditions, produce unstable dynamics manifesting as manic or depressive episodes. Endogenous perturbations (e.g., sleep–wake irregularity) or exogenous influences (e.g., psychosocial stress or treatment changes) can shift the system toward instability.

In this project, we implement a complex system-inspired predictive model that adapts the principles of Hadaeghi’s nonlinear dynamical framework to empirical actigraphy data. Rather than directly solving the system of equations, we estimate proxy indicators of system stability from the actigraphy signal. These indicators, which constitute the model’s features, will serve as a bridge between the abstract dynamical system and observed behavioural data.

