The extracted indicators will include statistical, time–frequency, and nonlinear features derived from the activity time series and computed over sliding temporal windows, yielding time-varying feature trajectories that reflect changes in system stability. Statistical features (e.g., mean, variance, skewness) will describe overall activity levels; time–frequency features (e.g., spectral power, rhythm amplitude, phase stability) will capture periodicity and circadian patterns; and nonlinear features (e.g., sample entropy, fractal dimension, Lyapunov exponent, correlation dimension, detrended fluctuation analysis) will quantify the complexity and predictability of rest–activity dynamics.

The predictive framework will be implemented using nonlinear dynamic modelling approaches, such as recurrent neural networks (RNNs) or nonlinear autoregressive models, which model sequences of time-indexed feature vectors and are, therefore, well-suited to capturing feedback relationships and temporal dependencies in evolving system dynamics. These models do not explicitly recover the underlying dynamical equations but are designed to learn temporal dependencies in the observed data. These data-driven models are conceptually aligned with Hadaeghi’s formulation of BD as an interacting dynamical system.

The model will be trained to identify patterns and trajectories in these features that precede critical transitions in system stability. In Studies 1 and 2, these transitions will correspond to relapse events among interepisode participants, while in Study 3 they will represent treatment response during acute manic or depressive episodes.

*Input and outcome variables for modelling*

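### Study 3 judges one pooled state-transition model on a mixed test set, which cannot show whether relapse and recovery share an instability signal

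*Protocol article*

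**What the plan says.** **Target and test set.** In Section 2.2 (Study 3), Research Question 1 asks how many Study 3 samples, x, must be added to the 75 Study 1 training samples. The aim is acceptable accuracy for one model "predicting both relapse amongst interepisode patients and response to treatment amongst acutely ill patients". Research Question 2 tests that model on a single unseen set of 25 Study 1 samples and 45 − x Study 3 samples. Section 2.6 sets the labels: in Studies 1 and 2 the transitions are relapses, "while in Study 3 they will represent treatment response during acute manic or depressive episodes".

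**Inference.** Section 2.2 says that, if generalisation is shown, one could hypothesise that the model "captures generic system instability (as opposed to a relapse-specific process".

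**Theory.** The Introduction describes "exploring system instability as a predictor of both relapse into, and recovery from acute episodes", which implies one direction for both. Section 2.6 says that relapse and "recovery from an acute episode both represent state transitions at which interacting biological and behavioural processes lose or regain stability", and that under some conditions the coupled subsystems "produce unstable dynamics manifesting as manic or depressive episodes". It assigns no direction to either transition.

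**Inputs and moderators.** Section 2.6 names actigraphy and derived features as the primary input. Starting state (interepisode or acute) is not named as an input. The only moderator in the research questions is depressive versus manic polarity within Study 3. Nothing in the article compares discrimination or indicator direction between relapse and response.

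**The concern.** Study 3's mechanistic contribution depends on what a successful pooled model means. At least three situations could produce good accuracy on the mixed set:

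1. Instability indicators rise before both relapse and recovery. This is the shared signal of interest.
2. Indicators are high before relapse but low before recovery, and a flexible model learns a separate mapping for each group. The wording about regaining stability and about episodes as unstable dynamics allows this.
3. The model has no stability signal. It recognises acute, mostly inpatient, actigraphy and exploits a difference in event rates between the cohorts.

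Only the first supports generic instability. Retraining sharpens the problem: once Study 3 labels enter training, good accuracy no longer shows that features found to predict relapse carry over to recovery.

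**Working it through.** The article gives no accuracy or power figure for the pooled model, so there is none to reproduce. The check asks what mixed-set AUC each situation would produce.

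**Inputs from the article.** The split is 75 + x for training and 25 + (45 − x) for testing. The Discussion gives 0.4 new episodes per year for BD I. As a consistency check, 0.4 × 1.5 years × 100 = 60, which matches its estimate of about 60 relapses.

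**Study 1 event rate, assuming a constant rate.** P(at least one relapse) = 1 − exp(−0.4t).
- 26 weeks: 1 − exp(−0.2) = 0.18. This applies if labels attach to actigraphy epochs, as Section 2.6 says.
- 78 weeks: 1 − exp(−0.6) = 0.45. This applies if labels attach to participants.

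**Assumptions not in the article.** Study 3 response is 50% or 70%, and x is 10, 20 or 30. There is one standardised stability indicator with log-odds slope 0.8 per SD (within-cohort AUC about 0.70), positive for relapse and either +0.8 or −0.8 for response. A logistic model stands in for the planned learner, with 1,500 simulated runs per setting.

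**Cohort recognition only, by hand (x = 20, so 25 + 25 tested; 18% versus 50%).**
- Expected events: 25 × 0.18 = 4.5 and 25 × 0.50 = 12.5. Share of events from Study 3: 12.5/17 = 0.735.
- Expected non-events: 20.5 and 12.5. Share of non-events from Study 3: 12.5/33 = 0.379.
- AUC = 0.5 + 0.5 × (0.735 − 0.379) = 0.678.

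The simulation gave 0.679. This assumes perfect recognition of the cohort; imperfect recognition would give less.

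**Simulated mixed-set AUC at x = 20:**

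| Study 1 rate | Study 3 rate | Same sign, one slope | Opposite signs, slope by cohort | No signal, cohort only |
|---|---|---|---|---|
| 18% | 50% | 0.681 | 0.744 | 0.679 |
| 18% | 70% | 0.654 | 0.808 | 0.767 |
| 45% | 50% | 0.702 | 0.680 | 0.506 |
| 45% | 70% | 0.694 | 0.713 | 0.625 |

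Over x = 10, 20 and 30 the ranges are 0.65–0.70, 0.65–0.81, and 0.66–0.77 (18%) or 0.51–0.63 (45%). The second column's model also has a cohort term, so its highest values partly reflect cohort recognition.

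**Within each cohort.**
- Cohort recognition alone gives AUC about 0.50 in both, so separate reporting exposes it.
- Opposite signs with cohort-specific slopes give about 0.70 in Study 1 and 0.64–0.69 in Study 3. Separate AUCs alone would therefore not reveal the reversal; direction must be compared as well.
- Opposite signs forced through one common slope give 0.62–0.70 in Study 1, 0.30–0.39 in Study 3 and 0.44–0.55 on the mixed set.

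**Precision in Study 3.** Take all 45 patients, 25 responders (assumed) and AUC 0.35. The Hanley–McNeil terms are Q1 = 0.35/1.65 = 0.212 and Q2 = 2 × 0.35²/1.35 = 0.181. The variance is [0.2275 + 24 × (0.212 − 0.1225) + 19 × (0.181 − 0.1225)]/500 ≈ 0.0070, so the SE is about 0.08 and the 95% interval roughly 0.19–0.51.

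**The case against.** **The theory is not contradictory.** A reader might infer that Section 2.6 equates relapse with loss of stability and recovery with its return, so that one positive label is wrong. The text does not go that far. The sentence covers both transitions together, and Section 2.6 has the model look for patterns that come before a transition. Instability preceding either shift is coherent, and on that reading a common label is right. This objection stands: the article is ambiguous, and opposite signs are only a possibility.

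**Cancellation need not happen.** A reader might infer that opposite effects cancel and Research Question 1 has no solution. That holds only for a model forced to one common slope. Section 2.6 plans recurrent neural networks or nonlinear autoregressive models, which can learn state-dependent effects. Their main risk is misreading. The two harms are also alternatives: where effects cancel, accuracy falls and no generic instability would be claimed.

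**The inference is hedged.** Section 2.2 offers a hypothesis, its premise concerns features found in Study 1, and Section 1.4 calls the project exploratory. This lowers the stakes. It does not repair the inference, because the research questions put that premise to the test through a retrained model and a mixed test set.

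**Detail can wait for the analysis plan.** Signs and model terms commonly sit there, and their absence here is no fault. But the pooled target, the mixed test set and the conclusion drawn from success are fixed in this article. The polarity analysis covers only part of the gap, since it compares depression with mania, not relapse with recovery.

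**Conclusion.** The point holds as a limit on what pooled accuracy can show. Under the stated assumptions, a mixed-set AUC near 0.7 is compatible with a shared signal (0.65–0.70) and with opposite effects learned separately (0.65–0.81). With an 18% Study 1 event rate, it is also compatible with no stability signal (0.66–0.77). At a 45% rate, cohort recognition alone is a weaker explanation (0.51–0.63), but the overlap between shared and opposite effects remains. These figures depend on the assumed slope, response rates and x, on a one-indicator logistic model, and on an episode rate reported for BD I alone.

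The documents do not show that the effects are opposite, that the planned models would cancel them, or that the sponsor would state the conclusion without its hedge. Nor would a Study 3 AUC below 0.5 establish regained stability: its interval is wide, and ward setting or treatment could also reverse an indicator.

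**What to change.** Before Study 3 outcomes are used, make these changes for Research Questions 1 and 2:

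- Define acceptable accuracy, and report discrimination, separately for Study 1 relapse and Study 3 response. The mixed-set figure may be added but should not decide the question.
- Report the unretrained Study 1 model (x = 0) in Study 3. This is the direct test of whether relapse features carry over.
- State in advance the expected direction of a short list of stability indicators for each transition, and compare the observed directions between cohorts.
- Suggest generic instability only if discrimination is present within both cohorts and the directions agree.
- Treat a reversed direction or an AUC below 0.5 as descriptive.

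No new data are needed, and the extra analysis is small. The price is imprecision: with at most 45 Study 3 patients, and fewer once x go to training, cohort-specific estimates will have wide intervals, and the honest answer may be that the question stays open. A full interaction by three starting states is not advisable, because one of them would rest on 15 manic patients.
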